## Abstract

**Abstract:**

**Introduction:**

Randomised controlled trials have aimed to assess the effectiveness of stereotactic ablative radiotherapy (SABR) with curative intent versus surgical resection for individuals diagnosed with early-stage non-small cell lung cancer (NSCLC) but have failed to recruit sufficient numbers of patients. Non-randomised studies for early-stage NSCLC have reported mixed outcomes following curative SABR versus surgical resection, but did not fully address confounding by indication. The Surgery Or RadioTherapy for early-stage cancer study (SORT) will assess the comparative effectiveness of SABR with curative intent versus surgical resection for NSCLC with a target trial emulation approach, as this can reduce biases in observational studies that aim to estimate the causal effect of interventions.

**Methods and analysis:**

The SORT study will use the National Cancer Registry for individuals diagnosed with early-stage NSCLC in England during 2015–2020 (inclusive) who received SABR with curative intent or surgical resection. These data will be linked to Hospital Episode Statistics, National Radiotherapy Data Set and the Systemic Anti-Cancer Therapy dataset to obtain information on clinical and sociodemographic characteristics and the treatment received. This target trial emulation will define study population eligibility criteria and regimens for SABR with curative intent and surgical resection. We will reduce the risk of residual confounding with instrumental variable analyses that will exploit geographical variation across the National Health Service in England in the use of SABR with curative intent versus surgical resection for early-stage NSCLC. The primary outcome will be 3-year all-cause mortality after treatment initiation. Secondary outcomes will include 3-month, 6-month, 12-month and 24-month all-cause and lung-cancer mortality, time to death, numbers of hospitalisations, incremental costs and incremental cost-effectiveness.

**Ethics and dissemination:**

Ethical approval was obtained from the London School of Hygiene and Tropical Medicine Research Ethics Committee (reference number 29 717–1). Results will be disseminated to clinicians, patients, policy-makers and researchers.

STRENGTHS AND LIMITATIONS OF THIS STUDYThe Surgery Or RadioTherapy (SORT) for early-stage cancer study will use a national cancer registry linked to treatment databases to provide evidence of comparative effectiveness of direct relevance to routine clinical practice.The integration of the target trial framework with the instrumental variable analysis will reduce the risk of confounding by indication.The national population-based cancer registry has limited detail on tumour location, so the surgical resection group may include patients such as those with centrally located disease, who might not have been eligible for SABR.The instrumental variable analysis relies on causal assumptions which can only be partly tested.

## Introduction

 Lung cancer is the leading cause of cancer deaths in England, accounting for 21% of all cancer deaths^1^, and survival is worse than in comparable countries.^2 3^ Non-small cell lung cancer (NSCLC) is the most common type of lung cancer (87.4%).^4^ Surgical resection is the standard of care for early-stage NSCLC with options that include lobectomy, pneumonectomy, bilobectomy or wedge resection.^5^ The National Institute for Health and Care Excellence (NICE) recommends stereotactic ablative radiotherapy (SABR)^5^ as an alternative to resection, recognising that SABR is well-tolerated and has better survival rates than conventional radical radiotherapy.^6^,^8^ NICE guidelines highlight the need for research comparing SABR to surgery, given that SABR is a non-invasive, organ-preserving treatment. If SABR is as effective as surgery, then it could be a preferable option for some people with NSCLC,^5^ while also helping to alleviate pressure on limited surgical resources and reduce waiting times. However, NICE guidelines also highlight the absence of unequivocal evidence on comparative effectiveness from randomised controlled trials (RCTs) comparing SABR vs surgical resection for early-stage NSCLC.

Several RCTs comparing SABR versus surgical resection for early-stage NSCLC, including ROSEL,^9^ STARS,^10^ SABRTooth^11^ and ACOSOG 4099/RTOG 1021,^12^ have closed prematurely because of slow accrual. This challenge is largely driven by patient and clinician preference for either treatment modality.^13^ A pooled analysis of the ROSEL and STARS trials suggested that SABR and surgical resection may result in similar 3-year overall and recurrence-free survival.^14^ However, the limited sample size and short follow-up meant that the findings were highly uncertain and difficult to interpret for clinical practice. Currently, two ongoing phase III RCTs, VALOR^15^ (accrual ongoing) and STABLEMATES^16^ (accrual completed), are investigating the comparative outcomes of SABR and surgical resection for early-stage NSCLC. Pending the results of these RCTs, clinical decision-makers and patients lack high-quality evidence to guide treatment decisions.

While SABR is typically recommended for individuals who are ineligible or who decline surgical resection, growing observational evidence suggests that, for some patients, SABR may offer similar outcomes to surgical resection.^17^ Several single-centre^18^,^21^ and multicentre^22 23^ non-randomised studies suggest that overall survival between 1 year and 5 years after diagnosis may be similar among individuals who receive SABR or surgical resection.^18 20 22^ One single-centre study reported higher cancer-specific survival, but lower overall survival following SABR versus surgical resection.^21^ Some meta-analyses of non-randomised studies have found similar lung-cancer-specific survival at 5 years,^24^ others that overall mortality is similar at 1–5 years after diagnosis,^25 26^ while a third group has reported that overall survival at 5 years is lower following SABR compared with lobectomy or sublobar resection.^24 27^ A major concern is that none of these studies have attempted to reduce the risk of unmeasured confounding, which may have led to biased estimates of comparative effectiveness and limited the studies’ relevance for clinical decision-making.

Evidence about the cost-effectiveness of SABR versus surgical resection for early-stage NSCLC is also limited. A recent systematic review by Maia *et al*^28^ identified six studies that compared the direct healthcare costs of SABR versus surgery. Two of the studies concluded that SABR was cost-effective compared with surgical resection,^29 30^ and the study by Puri *et al*^31^ found that surgery was more cost-effective than SABR, while other studies reported mixed results depending on the surgical procedures compared.^32^,^34^ The variation in results from these studies is likely driven by differences in study design, the surgical procedures compared, and the costs considered.^28^

This uncertainty in the evidence about the effectiveness and cost-effectiveness of SABR with curative intent versus surgical resection has contributed to variation across National Health Service (NHS) trusts in England in the proportion who received SABR for early-stage NSCLC.^4 35^ These variations may partly reflect differences in the preferences of thoracic oncology teams, the number of SABR centres which increased from approximately 20 (2015) to 37 (2019),^36^ and in the fitness and demographic of patients diagnosed with early-stage NSCLC.^17^ Older individuals, who represent the fastest growing subpopulation presenting with early-stage NSCLC,^37^ are more likely to have multiple long-term conditions and higher mortality rates,^38^ making them less suitable for surgical resection and more likely to receive SABR.^17^ During the COVID-19 pandemic, there was reduced surgical capacity, and so the uptake of radiotherapy, including SABR, increased in many centres.^39^,^41^

To address the challenges faced by previous non-randomised studies that have compared SABR to surgical resection for NSCLC, this study will leverage a national-level linked dataset and integrate a target trial emulation design with an instrumental variable analysis. The study will be designed to exploit the variations in use of SABR with curative intent across NHS trusts and over time to enable us to compare SABR with curative intent to surgical resection for similar patients who would be eligible for either modality. This approach aims to provide an accurate assessment of the comparative effectiveness and cost-effectiveness of SABR versus surgical resection for early-stage NSCLC.

### Aims and objectives

This study aims to evaluate the comparative effectiveness and cost-effectiveness of SABR with curative intent versus surgical resection for early-stage NSCLC, using cancer registry data from the National Disease Registration Service (NDRS) in England.^42^

The study objectives are:

To estimate the comparative effectiveness of SABR with curative intent versus surgical resection for the overall population and subgroups with early-stage (tumour: 1-2, node: 0, metastases: 0 (T1-2N0M0)) NSCLC.To evaluate the comparative cost-effectiveness of SABR with curative intent versus surgical resection for the overall population and subgroups with early-stage (tumour: 1-2, node: 0, metastases: 0 (T1-2N0M0)) NSCLC.

## Methods and analysis

### Overview

The SORT study will use large-scale linked national cancer registry data for England to evaluate the comparative effectiveness and cost-effectiveness of SABR with curative intent versus surgical resection for early-stage NSCLC over a 3-year follow-up period. We will integrate an emulated target trial design with an instrumental variable analysis to reduce the risk of confounding.^43^,^46^ Target trial emulation applies the design principles of RCTs to observational data in defining a hypothetical RCT (the emulated target trial) and can mitigate common design biases inherent in observational studies.^47^ In particular, our target trial will predefine patient eligibility, treatment strategies and outcomes. In stipulating these definitions, this protocol is informed by published and ongoing RCTs and non-randomised studies of SABR versus surgical resection for early-stage NSCLC, pilot data from the national cancer registry, and expert opinion from a clinical panel. The SORT NSCLC clinical panel comprised nine cardiothoracic surgeons and radiation oncologists who met online in April 2024 to inform the study protocol. Input from this panel focused on refining eligibility criteria, treatment definitions and anticipated effect sizes. The accompanying cost-effectiveness analysis (CEA) will assess whether SABR with curative intent versus surgical resection is cost-effective overall and for specific patient subgroups.

### Data

An overview of the datasets and their purpose is presented in table 1. We will use England’s NDRS Cancer Registry data to identify individuals aged 18 and over diagnosed with early-stage (T1-2N0M0) NSCLC in 2015–2020 inclusive. The Cancer Registry collects comprehensive data on all malignant tumours diagnosed in England recorded by NHS healthcare providers as part of routine care. These data include information on tumour and patient characteristics, geographical location, vital status (alive, deceased, emigrated or lost to follow-up), and for this study, it will use follow-up data until the end date of 31 December 2023.

**Table 1 T1:** Overview of the different datasets within the ‘NDRS linked data’ and their proposed use in the SORT target trial for NSCLC

Dataset	Purpose in the study
National Disease Registration Service (NDRS) Cancer Registry	Identify individuals diagnosed with T1-2N0M0 NSCLC between 2015 and 2020 (base case) and between 2015 and 2023 (alternative analyses) Obtain vital status Collect patient and tumour characteristics (e.g., age at diagnosis, income deprivation, sex, tumour stage, histology)
Hospital Episodes Statistics inpatient and outpatient	Identify individuals who underwent surgical resection within 6 months of diagnosis Collate resource use (e.g., hospitalisations, outpatient visits, surgical procedures) Collect measured confounders (e.g., comorbidities and frailty) Define time zero (date of curative surgery)
Radiotherapy Data Set	Identify individuals who received SABR within 6 months of diagnosis (base case) Collate use of different radiotherapy regimens Identify time zero (date of first dose or radiotherapy)
Systemic anti-cancer therapy	Collate use of different immuno-oncology and chemotherapy regimens including those with palliative intent
Cancer outcomes and services data set	Obtain Zubrod performance status

M, Metastases; N, node; NSCLC, non-small cell lung cancer; T, tumour.

NDRS Cancer Registry data is linked to the inpatient and outpatient Hospital Episodes Statistics (HES) for all patients treated by the NHS in England. HES data contain clinical information, such as diagnoses, medical procedures, patient’s sociodemographic characteristics and geographical information for all outpatient and inpatient visits in England. The registry is also linked to the Radiotherapy Data Set and Systemic Anti Cancer Therapy data which contain records of all radiotherapy and chemotherapy provided by the NHS (See table 1). From the NDRS Cancer Registry linked dataset (the ‘NDRS linked data’), we will obtain required information on patient, clinical and contextual measures, treatments received and outcomes. A detailed description of the NDRS linked data completeness is provided elsewhere.^48^

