### Target trial design

We will emulate a target trial by conceptualising this non-randomised study as if it were an RCT in clearly defining the eligibility criteria, study population and treatment regimens (table 2).^43 47^ These definitions are informed by ongoing and prematurely closed RCTs comparing the effectiveness of SABR versus surgical resection for early-stage NSCLC.^9 10 15 16 49^ Even after applying the target trial eligibility criteria, it is likely that unobserved confounders (e.g., tumour location) will remain imbalanced between the comparison groups. We will use an instrumental variable (IV) analysis to reduce the risk of bias due to unobserved confounding^44 46 50^ (see the Analyses section for details).

**Table 2 T2:** Overview of the emulated target trial components and their definitions

Protocol component	Emulation protocol
Inclusion criteria	People with first primary NSCLC diagnosis (T1 – T2 N0 M0) between 1 January 2015 and 31 December 2020, according to ICD-10 C34 (all ICD-O-3 morphology codes except those between 8041 and 8045) who received SABR with curative intent or underwent surgical resection within 30 days before or 6 months after diagnosis (base case)
	Aged 18–79 years old if Zubrod performance status 0–2, age 80+if Zubrod performance status 0–1
Exclusion criteria	Synchronous lung cancerPregnancy at time of diagnosis
	Previous thoracic radiotherapy within 5 years prior to diagnosisPrevious metastatic malignancy within 5 years prior to diagnosis
	No surgery or radiotherapyOther types of radiotherapy as index treatment
Treatment strategies	Radiotherapy with curative intent: Stereotactic Ablative Radiotherapy (SABR)Surgical resection: Video-assisted or open thoracic lobectomy+/-mediastinal lymph node dissection (MLND); segmentectomy+/-MLND; wedge resection+/-MLND
Assignment procedure	Two approaches to address confounding: Randomisation will be emulated with an instrumental variable analysis that aims to balance observed and unobserved baseline prognostic measures between the comparison groups (base case analysis). The proposed instrument is the proportion of eligible patients treated with SABR versus surgical resection within the cancer network Randomisation will be emulated via a double robust method- inverse probability of treatment weighting with regression adjustment (alternative analysis)
Time zero	Date of treatment start

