Follow-up	Follow-up begins on date of treatment assignment (time zero) and ends 3 years after baseline (base case)
Outcome	Primary outcome: all-cause mortality at 3 years from the date of treatment receipt
	Secondary outcomes: all-cause and lung-cancer mortality at 3 months, 6 months, 12 months, 24 months, and 36 months; time to death; number of days in hospital in 12 months after treatment start; incremental costs; and incremental cost-effectiveness (incremental net health benefits).
Causal contrast of interest	Intention-to-treat effect (patients analysed according to their allocated treatment, regardless of whether they did not fully adhere to treatment or switched to other treatments)

NDRS, National Disease Registration Service; NSCLC, non-small cell lung cancer.

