#### Follow-up period and outcomes

The primary outcome is all-cause mortality 3 years from the start of treatment (time zero). We will also report all-cause and lung-cancer specific mortality at 3 months, 6 months, 12 months, 24 months and 36 months as secondary outcomes. We will define lung-cancer attributable mortality as those deaths which include lung cancer (International Classification of Diseases-10: C34) as a cause of death. Multivariable flexible hazard models^54^,^56^ will be fitted to estimate the effect of SABR versus surgical resection on time to death for both all-cause and lung-cancer specific mortality. For these time-to-death analyses, individuals treated during 2015–2023 inclusive will be included to maximise follow-up duration.

The number of days in hospital in the 12 months after the start of treatment will be recorded. We will use information on reasons and route of admission (eg, via emergency room) in the 90 days following the start of treatment to identify admissions attributable to grade three or four adverse events following either treatment modality (see also CEA).

In the pilot NDRS linked registry data, information was available for the primary endpoint (3-year mortality) for each individual in the eligible population. Covariate information was also complete for all the required covariates for the eligible population with the exception of ethnicity, for which the proportions with missing data were low and similar between the comparison groups (1.71% for SABR and 1.34% for surgical resection). The analysis will therefore use observations with complete case information which assumes the missing ethnicity data are independent of the outcome given the covariates included in the analytical models.^57^

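### Base-case patients treated in January to June 2021 and alive on 31 December 2023 have unknown 3-year status, because eligibility runs on diagnosis date but the outcome clock starts at treatment

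*Protocol article*

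**What the plan says.** All references are to the protocol article.

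- **Who is in (Table 2, inclusion criteria).** Eligibility is set by diagnosis date: "People with first primary NSCLC diagnosis (T1 – T2 N0 M0) between 1 January 2015 and 31 December 2020". The treatment window hangs on that date: "who received SABR with curative intent or underwent surgical resection within 30 days before or 6 months after diagnosis (base case". The Eligibility criteria and Treatment strategies sections repeat the 6-month allowance.
- **When the clock starts and stops (Table 2; Follow-up period and outcomes).** "The primary outcome is all-cause mortality 3 years from the start of treatment (time zero"), and "Follow-up begins on date of treatment assignment (time zero) and ends 3 years after baseline (base case").
- **When the data stop (Data).** "it will use follow-up data until the end date of 31 December 2023".
- **Censoring (Causal contrast of interest).** Base-case patients contribute until death or the end of 3 years. The date 31 December 2023 is named only for the alternative analysis.
- **Completeness (Follow-up period and outcomes).** In the pilot data "information was available for the primary endpoint (3-year mortality) for each individual in the eligible population". The pilot covers diagnoses in 2015–2018. The complete-case rule that follows is argued from missing ethnicity.
- **Model (Main analyses).** Mortality at 3 years is given as an example of a binary endpoint in the second-stage outcome model.

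**The concern.** The cohort is closed on one date (diagnosis) and the outcome is timed from another (treatment), which may fall up to 6 months later. The data end exactly 3 years after the last eligible diagnosis, not 3 years after the last eligible treatment. For patients treated in 2021, what is known at the cut-off depends on the outcome: deaths up to that day are recorded, while survivors have not yet reached 3 years.

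A binary 3-year endpoint needs a rule for these survivors, and the base case states none. The pilot completeness statement does not help, because treatment for 2015–2018 diagnoses started by mid-2019 at the latest.

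The gap also touches 36-month lung-cancer mortality and the 3-year life years, QALYs and costs. It falls entirely on 2020 diagnoses, and year of diagnosis is a prespecified subgroup. The mortality time points up to 24 months are not affected.

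**Working it through.** **1. Dates.**
- Latest time zero: 31 December 2020 + 6 months = about 30 June 2021.
- Its 3-year point: about 30 June 2024.
- Follow-up available to 31 December 2023: 914 days = 2.50 years.
- Full 3-year follow-up needs time zero no later than 31 December 2020. Any later start is short by 1 day to about 6 months.

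**2. How many.** The Sample size calculations section expects at least 18 000 patients (3000 SABR, 15 000 surgery) over six years. Taken as even, that is 3000 a year (500 and 2500). The document gives no waiting times, so the wait *w* (days from diagnosis to treatment) is an assumption. Number affected = 3000 × *w*/365.

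| Assumed wait | Affected | Share of 18 000 | Mean shortfall |
|---|---|---|---|
| 30 days | 247 | 1.4% | 15 days |
| 60 days | 493 | 2.7% | 30 days |
| 90 days | 740 | 4.1% | 45 days |
| every wait about 6 months (bound) | about 1490 | 8.3% | 91 days |

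**3. Effect on the crude risk difference.** Inputs are surgery 3-year mortality of 19.8% (pilot figure) and SABR 27.3% (19.8% plus the 7.5-point target difference, used for illustration). A constant hazard is assumed, *h* = −ln(1 − *p*)/3. In one arm with *n* diagnoses in 2020, *a* = *n* × *w*/365 are affected. Their shortfall is spread evenly over 0 to *w* days, and *q* is the average of 1 − exp(−*h*(3 − shortfall)), the chance that a death is seen.

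- Rule A, keep deaths and drop survivors of unknown status: risk = [(*n* − *a*)*p* + *aq*] / [(*n* − *a*) + *aq*].
- Rule B, count unknowns as alive: risk = [(*n* − *a*)*p* + *aq*] / *n*.

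For the whole cohort, add the other five years: 2500 SABR with 682.5 deaths and 12 500 surgery with 2475 deaths.

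Worked example under rule A, waits of 60 days (SABR) and 30 days (surgery):
- SABR: *a* = 82.2, *q* = 0.2666. For 2020, 135.97/439.7 = 30.9%. Overall, 818.5/2939.7 = 27.8%.
- Surgery: *a* = 205.5, *q* = 0.1956. For 2020, 494.5/2334.7 = 21.2%. Overall, 2969.5/14 834.7 = 20.0%.
- Difference: 9.7 points in 2020 diagnoses and 7.8 overall, against a true 7.5.

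The same formulas for all nine pairs of waits give these shifts in the difference, in percentage points:

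| SABR / surgery wait (days) | A: overall | A: 2020 | B: overall | B: 2020 |
|---|---|---|---|---|
| 30 / 30 | +0.05 | +0.3 | 0.00 | -0.01 |
| 60 / 60 | +0.11 | +0.7 | 0.00 | -0.02 |
| 90 / 90 | +0.16 | +1.1 | -0.01 | -0.06 |
| 60 / 30 | +0.3 | +2.2 | -0.01 | -0.08 |
| 90 / 60 | +0.4 | +2.8 | -0.03 | -0.16 |
| 90 / 30 | +0.6 | +4.4 | -0.04 | -0.22 |
| 30 / 60 | -0.16 | -1.2 | +0.01 | +0.05 |
| 60 / 90 | -0.11 | -1.1 | +0.01 | +0.08 |
| 30 / 90 | -0.4 | -3.0 | +0.03 | +0.15 |

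The 30 / 90 row under rule A: for 2020, SABR 136.4/470.0 = 29.0% and surgery 490.5/2001.1 = 24.5%. Overall, 818.9/2970.0 = 27.6% and 2965.5/14 501.1 = 20.4%.

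**4. Cost of capping time zero.** Losing 1.4% to 4.1% leaves about 17 750 to 17 260 patients, and the 8.3% bound leaves about 16 500. The largest total in Table 4 is 7110. A two-proportion calculation with the effect diluted by the assumed compliance of 0.7 gives power for a 5-point difference of at least 98% even at 16 500.

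**The case against.** Several points on the other side stand.

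- **A reader might infer that the primary outcome is unobservable for everyone treated in 2021.** It is not. Deaths up to the cut-off are recorded, and with waits of 30 to 90 days the mean shortfall is 15 to 45 days out of about 1095. Six months is the extreme.
- **A reader might infer that the plan keeps the deaths and drops the survivors.** It does not say so. The complete-case sentence is reasoned from missing ethnicity. Leaving out everyone without 3 years of potential follow-up would be a natural implementation. It selects on treatment date, not on outcome, and so avoids this bias.
- **A reader might infer a material, one-directional bias in the main result.** The larger shifts need both the unfavourable rule and a difference in waits between arms. The document gives no waits by arm, and reversing them reverses the sign. All the shifts are crude contrasts; the base case is a two-stage instrumental variable analysis, whose movement depends on how the missing status relates to the instrument.
- **Other wording hints at a limit by treatment year.** The sample size section speaks of pilot diagnoses and treatments in 2015–2018 and of an analysis sample for 2015–2020. The time-to-death analyses define their sample by treatment date, and hazard models can accommodate administrative censoring.

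The last point does not remove the conflict. Table 2 and the Eligibility criteria section set the base case by diagnosis date plus 6 months, nothing caps treatment date, and the hazard models serve the secondary time-to-death analyses. Nor is this detail that an article leaves to a fuller document: the article itself fixes dates that do not fit together.

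**Conclusion.** The point holds as a date conflict in the definition of the primary outcome. It follows from the protocol's own dates and needs no assumption.

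Its size does rest on assumptions: even accrual, a common wait within each arm, a constant hazard and a true difference of 7.5 points. Over waits of 30 to 90 days, dropping survivors shifts the crude difference by about -0.4 to +0.6 points overall and -3.0 to +4.4 points in 2020 diagnoses. Counting unknowns as alive shifts it by less than 0.1 and by about 0.2 or less, respectively. The documents do not support a claim that the overall result is seriously biased or that power is at risk. The 2020 subgroup is where poor handling could matter. This is a should-fix, with high confidence in the dates and low confidence in any single bias figure.

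**What to change.** Choose one, and state it in Table 2:

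1. Limit base-case time zero to no later than 31 December 2020, for all patients whatever their outcome. This is one added sentence and costs about 1.4% to 4.1% of patients on the assumed waits, with power barely affected.
2. If a later extract can be obtained, extend vital status and Hospital Episode Statistics to 30 June 2024. No patients are lost; the cost is the extra extract.

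Apply the same limit to 36-month lung-cancer mortality and to the 3-year cost-effectiveness analysis. Then align the Data section, the inclusion, follow-up and outcome rows of Table 2, and the censoring sentence under Causal contrast of interest. State also that the pilot completeness statement applies to 2015–2018 diagnoses only.
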